### Power analysis

The number of parents recruited for this study is 302. However, the effective sample size is less than this because we have intra cluster correlation (ICC), the value of which is unknown. The required effective sample size to detect a moderate effect size (d = 0.5) with 5% significance and 80% power is 102, which suggests that the sample size recruited is adequate as long as attrition rates are less than 50%, when the ICC is 3% (or less than 33% when the ICC is 6%).

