### Randomisation

At the end of the Time 1 questionnaire collection period, services (clusters) were randomised to the intervention or wait-list control group. Services varied in size (i.e., number of families and staff), location, and their National Quality Standard (NQS) status and it is possible these characteristics could have an impact on outcomes (e.g., some larger services might have more resources than others). To control for possible influence of these characteristics, we used a stratified randomisation procedure to increase the similarity of the intervention and control groups. Stratified randomisation was a two-stage procedure [18]:

First, the project team matched every service with another by examining the following factors: location of service, size of service (number of staff and number of families), and their NQS status (their overall rating and their Quality Area 6 rating). This resulted in eight matched pairs as well as three small rural services grouped into one cluster, without a match. We decided to include the rural cluster in the study because their responses would still be valuable for analyses. For the purposes of randomisation for this rural cluster a ‘dummy site’ was used as their match, as the ninth pair, so that the services in the rural cluster were randomised to the intervention or wait-list control group the same way as all other services. To begin the second stage of randomisation we used the online software random.org [19] to create a random number order. An independent researcher at the PRC, who was unaware of the names or locations of services, performed the random number generation and assignment of pairs. Before the researcher began the randomisation procedure, we allocated each service an alphabetical letter. A random order of numbers from one to nine was generated, then, moving down the matched pairs list, the first random number was allocated to the first member of the first pair. This continued until the first member of every pair had a random number. Services with numbers one to five were allocated to the intervention group. Their pair was allocated to the control group. Services with numbers six to nine were allocated to the control group. Their pair was allocated to the intervention group. This process ensured each service had a 50% chance of being allocated to the intervention group.

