### Baseline analysis (time 1)

As a check for appropriate balance between the control and intervention groups and to provide an overview of the study population [24], both at service and individual levels, data for the control and intervention groups will be compared at baseline. We will present the mean, standard deviation and range for continuous, approximately symmetric variables; medians, interquartile range and range for continuous, skewed variables of clusters. We will describe categorical data with percentages across sub-groups.

All statistical tests and confidence intervals will be two-sided. Between-group comparisons will be presented with 95% confidence intervals and the statistical significance level set will be at the 5% level. In addition, we will account for the clustered nature of the data for all comparative analyses to ensure correct confidence intervals and type I error rates are calculated. In addition, the intra-cluster correlation coefficient for each outcome, based on the adjusted analyses with 95% confidence interval, will be reported.

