### Analysis of primary and secondary outcome measures

An intention-to-treat multi-level analysis will be conducted for each of the outcome measures with level 1 data reflecting each assessment period, level 2 data reflecting individual participants and level 3 data reflecting the various services. Changes in the outcome measures will be compared for the intervention and control groups assuming appropriate distributions for the outcome measures. Random intercepts will be assumed, while allowing for the clustered nature of the data, and adjusting for appropriate covariates as fixed effects. The model will include an indicator variable for the study groups (0 = control, 1 = intervention) as a fixed effect at level 3 and an integer time variable (1 = baseline, 2 = time2 and 3 = time3) as a random effect at level 1.

We will report the estimated intervention effect as mean outcome difference for continuous outcomes and odds ratio for binary outcomes between intervention and control groups with 95% confidence intervals and *p*-values [25]. The effect of individual moderators will be incorporated using interaction terms between time, allocated group and the individual moderators [26].

Finally, a completer analysis will be conducted with a repeated measures MANOVA analysis using inverse probability weights to adjust for any attrition bias [27]. This analysis will also account for the correlation between measures from the same participant, while allowing for the clustered trial design.

Furthermore, we will examine responses of the control group before and after receiving the intervention.

As an indication of family-centredness, we will look at items that both educators and parents completed, to compare their perceptions (e.g. whether they both agree the service is a welcoming environment for parents).

All qualitative data (open text questions) will be summarised and examined for themes. Thematic analysis is a multi-stage process involving familiarisation with the data, coding (identifying important features relevant to the research questions), searching for and reviewing themes, and defining and naming them [28].

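### The power paragraph tests individuals one-sidedly and treats clustering only as a variance discount; on its own single-timepoint basis, two-sided power at the stated attrition limits is about 73-76%, not 80%

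*Protocol article*

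**What the plan says.** The Power analysis section of the protocol article starts from 302 recruited parents, notes that the intra-cluster correlation is unknown and makes the effective sample size smaller, and gives the target: "The required effective sample size to detect a moderate effect size (d = 0.5) with 5% significance and 80% power is 102". It concludes that recruitment is "adequate as long as attrition rates are less than 50%, when the ICC is 3% (or less than 33% when the ICC is 6" (the last figure is also a percentage). It does not mention the number of randomised units, variation in service size, a baseline correlation or the side of the test.

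Four other statements bear on this:

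- Randomisation, on the units: "This resulted in eight matched pairs as well as three small rural services grouped into one cluster, without a match". Eight pairs are 16 services. With the rural group allocated as one unit, that makes 17 real units; the dummy site contributes no data. Counted singly there are 19 services.
- Randomisation, on size: "Services varied in size (i.e., number of families and staff), location, and their National Quality Standard (NQS) status".
- Baseline analysis (time 1), worded for the whole trial although it stands under that heading: "All statistical tests and confidence intervals will be two-sided".
- Analysis of primary and secondary outcome measures: "The model will include an indicator variable for the study groups (0 = control, 1 = intervention) as a fixed effect at level 3". Level 3 is the service.

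**The concern.** A design effect corrects the variance of the arm difference. It does not supply the degrees of freedom with which that variance is estimated. When about 100 independent people are compared, the t reference is nearly normal. When 17 or 19 services are compared, it has 15 or 17 degrees of freedom and a larger critical value, so the same effective sample size buys less power. An equal-size design effect also understates the variance when services contribute different numbers of parents. Separately, the target itself appears to be one-sided in a trial whose tests are two-sided.

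The paragraph's attrition limits are what a reader will use to judge the result. Parent satisfaction with educator interactions is a primary outcome. If it shows no effect with attrition inside the limits, the trial would be described as adequately powered on a calculation that does not support the description.

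**Working it through.** **Inputs from the protocol.** d = 0.5, 5% significance, 80% power, required effective size 102, 302 parents, ICC 3% with 50% attrition and ICC 6% with 33% attrition (Power analysis); 17 units or 19 services (Randomisation, Participants); two-sided tests (Baseline analysis).

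**Assumptions.** Equal numbers of parents per arm, since numbers by arm are not given. The coefficient of variation (CV) of cluster size is also not given; it is taken as 0 first, then 0.4 to 0.6.

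**1. Reproducing 102.** For a two-sample t-test at d = 0.5 and 80% power:

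- One-sided 5%: 50.15, rounded up to 51 per arm, total 102. Power at 102 on 100 df is 80.6%.
- Two-sided 5%: 63.77, rounded up to 64 per arm, total 128. Two-sided power at 102 on 100 df is 70.6%.

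So 102 is the one-sided figure for individuals.

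**2. Reproducing the attrition limits.** With k clusters and the design effect held at the recruited cluster size, DE = 1 + (302/k - 1) x ICC, and the limit is 1 - 102/(302/DE).

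| k | ICC 3% | ICC 6% |
|---|---|---|
| 17 | 49% | 32% |
| 18 | 50% | 34% |
| 19 | 51% | 36% |
| Printed | 50% | 33% |

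The printed limits therefore come from an equal-size design effect applied to the target of 102.

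**3. Power at those limits on cluster degrees of freedom.** Take n = 302 x (1 - attrition), m = n/k, DE = 1 + ((1 + CV^2) x m - 1) x ICC and effective size = n/DE. The noncentrality is 0.5 x sqrt(effective size)/2, with a two-sided 5% noncentral t on k - 2 df. Here DE is recomputed after attrition, which favours the plan, and CV = 0.

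| Units | ICC, attrition | n | m | DE | Effective size | Power |
|---|---|---|---|---|---|---|
| 17 (15 df) | 3%, 50% | 151 | 8.88 | 1.236 | 122.1 | 73.3% |
| 17 (15 df) | 6%, 33% | 202.3 | 11.90 | 1.654 | 122.3 | 73.4% |
| 19 (17 df) | 3%, 50% | 151 | 7.95 | 1.208 | 125.0 | 75.0% |
| 19 (17 df) | 6%, 33% | 202.3 | 10.65 | 1.579 | 128.1 | 76.0% |

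If DE is held at the recruited cluster size, as the printed limits imply, the effective size is 100.5 to 106.8 and power is 65-68%.

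**4. Sidedness alone is not the repair.** An effective size of 128 gives 80.1% on 126 df, but 75.3% on 15 df and 76.0% on 17 df. For 80% the required effective size is about 144 (15 df) or 142 (17 df).

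**5. Limits that keep 80%** (equal sizes, DE recomputed after attrition). ICC 3%: about 38% (17 units) or 42% (19 services). ICC 6%: about 9% or 20%.

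**6. Unequal sizes, as a range only.** At the stated limits, an assumed CV of 0.4 to 0.6 gives 70-74% at ICC 3% and 67-73% at ICC 6% across the two unit counts.

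**The case against.** The strongest reply is that this is not the comparison the trial will make. Trial outcomes and the analysis section describe change over time, analysed in a three-level model with repeated assessments and random intercepts. A service intercept cancels from a change contrast, so the group-by-time effect need not be tested against the full between-service variation, and use of the baseline can reduce variance. If adjustment cuts the variance by 1 - r^2, equal-size power at the stated limits becomes 77-80% for r = 0.3, 80-83% for r = 0.4 and 85-87% for r = 0.5. These r values are assumed; the protocol gives none. This stands: a reader might infer from the 73-76% that the planned analysis is underpowered, and the document does not show that. But the power paragraph claims no such gain, so its statement of adequacy cannot rest on it.

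Second, the fall below 80% needs the two-sided rule. With a one-sided 5% test, step 3 gives 84-86% on cluster degrees of freedom. This also stands, but the protocol fixes two-sided testing, and step 4 shows that both corrections are needed.

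Third, the document does not settle 15 degrees of freedom. Trial design and the model treat each service as a cluster, which points to 19, and a pair-matched analysis would have fewer degrees of freedom, offset by any variance that matching removes. So the result is a range, and 38% and 9% should not be imposed as the only limits.

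Fourth, the unequal-size figures rest on an assumed CV. With CV 0.6 and ICC 6%, power is 75-78% even without attrition. A reader might conclude that the trial misses 80% from the outset. The protocol says that services vary in size but gives no parent counts, so that conclusion is not supported.

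**Conclusion.** The concern holds for the power paragraph as written. Its target is one-sided and for individuals, and its allowance for clustering leaves out the number of units and the variation in their size. On its own basis, two-sided power at its limits is about 73% (17 units) to 75-76% (19 services), a shortfall of 4 to 7 points. This rests on equal service sizes, equal parents per arm, a design effect recomputed after attrition, units minus 2 degrees of freedom and no credit for baseline. Holding the design effect at the recruited cluster size gives 65-68%; unequal sizes also lower the power; credit for baseline would raise it. The ICC 6% limit is the most affected, falling from 33% to between 9% and 20%.

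This is a fault in the stated justification. It does not show that the trial is too small or that the planned model is wrong. The choice of a small-sample degrees-of-freedom method for that model is detail that an analysis plan may supply, and its absence from the article is not held against it.

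**What to change.** Restate the power paragraph as follows:

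1. Use a two-sided 5% t reference with cluster-level degrees of freedom, and state whether 17 units or 19 services are counted. The required effective size is then about 144 or 142 in place of 102.
2. Use the design effect 1 + ((1 + CV^2) x mean size - 1) x ICC, with the CV taken from the Time 1 parent counts and the mean size taken after attrition.
3. Replace the 50% and 33% limits with the resulting ranges: with equal sizes about 38-42% at ICC 3% and 9-20% at ICC 6%, lower once the observed CV is entered.
4. If credit is taken for baseline or repeated measures, state the assumed correlation and show power over a range of it.

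The cost is one rewritten paragraph and a short calculation from counts already collected. The stated adequacy may become less favourable. No further recruitment or data are needed, and Trial status reports that follow-up is still to come, so the change can be made before the results are interpreted.

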### Participants

Participants are educators and parents recruited from the 19 participating ECEC services. Out of 276 educators employed at these services at the time of recruitment, 118 gave consent to take part in the trial by completing the Time 1 questionnaire. Educators included kindergarten teachers with university (tertiary) qualifications and early childhood educators with a range of qualifications, such as certificates, diplomas and bachelor’s degrees. Services required all educators to implement the intervention whether or not they agreed to take part in the anonymous and voluntary evaluation component (the trial).

Out of 1471 families who had at least one child enrolled in one of the 19 services, 302 parents consented to take part and completed the Time 1 questionnaire.

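### The required effective sample size of 102 is the one-sided figure; the plan's two-sided 5% tests need 128, so the attrition limits presented as following from 102 must be re-derived

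*Protocol article*

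**What the plan says.** The Power analysis section starts from the parent sample: "The number of parents recruited for this study is 302". It notes that clustering lowers the effective size and that the ICC is unknown. It then says that the effective sample needed for d = 0.5 "with 5% significance and 80% power is 102, which suggests that the sample size recruited is adequate", on condition that attrition is under 50% at an ICC of 3%, or under 33% at an ICC of 6%. The section does not give the sidedness of the test, the number of clusters, the design-effect formula, the degrees of freedom or any correlation with baseline.

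Sidedness is fixed in the section Baseline analysis (time 1): "All statistical tests and confidence intervals will be two-sided", and "the statistical significance level set will be at the 5% level".

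On clusters, the Participants section says: "Participants are educators and parents recruited from the 19 participating ECEC services". Trial design treats each service as a cluster, and the outcome model places services at level 3. The Randomisation section, however, describes eight matched pairs plus three small rural services grouped as one unit and paired with a dummy site. That makes 8 × 2 + 1 = 17 real randomised units, or 18 with the dummy site.

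**The concern.** The figure of 102 is familiar as the one-sided answer to this sample-size question, while the article commits to two-sided testing. This paragraph is the article's only quantitative support for calling 302 parents enough. Time 2 data were being collated and follow-up was still to come at the time of writing, so readers will judge retention against the 50% and 33% limits. If the base figure is too low, those limits may be too generous, and a null result could be read as coming from a trial with 80% power when it had less.

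**Working it through.** **Inputs.** d = 0.5, 80% power, 102, 302 parents, ICC 3% and 6%, limits 50% and 33% (Power analysis); two-sided 5% (Baseline analysis); 19 services (Participants); 17 or 18 randomised units (Randomisation). Assumed here: equal arms and equal cluster sizes.

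**Step 1: reproduce 102.** Two-sample t-test with n per arm, noncentrality d·√(n/2), df = 2n − 2:

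| Test at 5% | n per arm | Total | Power |
|---|---|---|---|
| One-sided | 51 | 102 | 80.6% |
| Two-sided | 64 | 128 | 80.1% |
| Two-sided, at the stated total | 51 | 102 | 70.6% |

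The normal approximation gives totals of 100 (one-sided) and 126 (two-sided). So 102 matches the one-sided t-test exactly and neither two-sided figure.

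**Step 2: could baseline adjustment explain 102?** Adjustment multiplies the requirement by 1 − r². Solving 128(1 − r²) = 102 gives r = √(1 − 102/128) = 0.45. The article states no such correlation.

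**Step 3: attrition limits with cluster size held at its recruited value.** With k clusters and m = 302/k, the design effect is DE = 1 + (m − 1)·ICC, the effective size is 302/DE, and the limit is 1 − required/effective. For k = 17: m = 17.76, DE = 1.503 (ICC 3%) and 2.006 (ICC 6%), effective sizes 200.9 and 150.6.

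| k | From 102: ICC 3% / 6% | From 128: ICC 3% / 6% |
|---|---|---|
| 17 | 49.2% / 32.3% | 36.3% / 15.0% |
| 18 | 50.2% / 34.3% | 37.6% / 17.5% |
| 19 | 51.1% / 36.0% | 38.7% / 19.7% |

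With 17 or 18 units, 102 comes close to the stated 50% and 33%, though no row matches both exactly.

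**Step 4: limits when cluster size falls with dropout.** If N parents remain, the effective size is N/[1 + (N/k − 1)·ICC]. Setting this equal to the requirement R gives N = R(1 − ICC)/(1 − R·ICC/k), and the limit is 1 − N/302. For R = 128, k = 19, ICC 6%: N = 128 × 0.94/(1 − 128 × 0.06/19) = 202.0, a limit of 33.1%.

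| k | From 102: ICC 3% / 6% | From 128: ICC 3% / 6% |
|---|---|---|
| 17 | 60.0% / 50.4% | 46.9% / 27.3% |
| 18 | 60.5% / 51.9% | 47.7% / 30.5% |
| 19 | 60.9% / 53.2% | 48.5% / 33.1% |

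Here the printed limits are close to those for 128 with 19 services, and far from those for 102.

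**Step 5: two-sided power at the printed limits (50% at ICC 3%; 33% at ICC 6%).**

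| Route | Effective size | Power |
|---|---|---|
| Fixed cluster size, k = 17 | 100.5 / 100.9 | 69.9% / 70.1% |
| Fixed cluster size, k = 19 | 104.4 / 106.8 | 71.6% / 72.6% |
| Shrinking, k = 17 | 122.1 / 122.3 | 78.2% / 78.3% |
| Shrinking, k = 19 | 125.0 / 128.1 | 79.2% / 80.2% |
| Shrinking, k = 17, t on 15 df | 122.1 / 122.3 | 73.3% / 73.4% |
| Shrinking, k = 19, t on 17 df | 125.0 / 128.1 | 75.0% / 76.0% |

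The last two rows use k − 2 degrees of freedom, a choice made here because the article specifies none.

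**The case against.** A reader might infer that both printed attrition limits are wrong, and that figures such as 36% and 15% should replace them. The documents do not support that. The Power analysis section states neither the cluster count nor the design-effect method. The route that yields 36% and 15% is an inference: it takes 17 units, although the article calls each of 19 services a cluster, and it holds cluster size fixed while parents drop out. When parents leave and services stay, the mean cluster size falls. Allowing for that, with 19 services, the two-sided requirement of 128 gives 48.5% and 33.1%, practically the printed values, and power there is 79.2% and 80.2% before any allowance for few clusters. This part of the objection stands.

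It does not rescue the paragraph. If the limits were obtained from 102, as the sentence presents them, the only route tried here that comes near them holds cluster size fixed, and 128 then lowers them. If they allow for shrinking clusters, they do not follow from 102, which would give about 60–61% and 50–53%. Either way the requirement and the limits need to be reconciled.

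It can also be said that the covariate-adjusted multilevel model may gain enough precision to make 102 sufficient. That is possible at a baseline correlation of about 0.45, but the paragraph claims no such credit. Finally, recruitment is closed and no test or estimate changes. That limits the consequence, not the error.

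The small-degrees-of-freedom results are a separate argument from the sidedness error and depend on how the model is tested. They show only that the favourable route is itself sensitive to the small number of clusters.

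**Conclusion.** Wrong as written. Under the article's own two-sided 5% rule, the required effective sample for d = 0.5 and 80% power is 128, not 102, and 102 gives about 71% power. This rests only on the stated inputs and equal arms, and is certain.

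For the attrition limits, what is established is narrower: they do not validly follow from 102 under two-sided testing. Their corrected values depend on an unstated method. For 17 to 19 clusters they are about 36–39% (ICC 3%) and 15–20% (ICC 6%) with cluster size fixed, or about 47–48.5% and 27–33% with cluster size falling. Tests on 15 to 17 degrees of freedom would put power at the printed limits at about 73–76% even on the more favourable route. All of these assume equal cluster sizes; unequal sizes would lower them further.

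**What to change.** In the Power analysis section, state that the calculation is two-sided and replace 102 by 128. Alternatively, keep 102 and state and justify the baseline correlation (about 0.45) that would support it. If a one-sided calculation was intended, say so and reconcile it with the two-sided rule.

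Then re-derive both attrition limits and show what they rest on: the cluster count (19 services or 17 randomised units), whether the design effect uses the recruited or the retained cluster size, and the degrees of freedom assumed. The ranges above should not be pasted in as replacements, because they span several methods.

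The cost is one corrected paragraph, with limits that may become less favourable. No further recruitment and no change to the planned analysis is needed.
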